## Abstract

**Background::**

Early reversion of sepsis-induced tissue hypoperfusion is essential for survival in septic shock. However, consensus regarding the best initial resuscitation strategy is lacking given that interventions designed for the entire population with septic shock might produce unnecessary fluid administration. This article reports the rationale, study design and analysis plan of the ANDROMEDA-2 study, which aims to determine whether a peripheral perfusion-guided strategy consisting of capillary refill time-targeted resuscitation based on clinical and hemodynamic phenotypes is associated with a decrease in a composite outcome of mortality, time to organ support cessation, and hospital length of stay compared to standard care in patients with early (< 4 hours of diagnosis) septic shock.

**Methods::**

The ANDROMEDA-2 study is a multicenter, multinational randomized controlled trial. In the intervention group, capillary refill time will be measured hourly for 6 hours. If abnormal, patients will enter an algorithm starting with pulse pressure assessment. Patients with pulse pressure less than 40mmHg will be tested for fluid responsiveness and receive fluids accordingly. In patients with pulse pressure > 40mmHg, norepinephrine will be titrated to maintain diastolic arterial pressure > 50mmHg. Patients who fail to normalize capillary refill time after the previous steps will be subjected to critical care echocardiography for cardiac dysfunction evaluation and subsequent management. Finally, vasopressor and inodilator tests will be performed to further optimize perfusion. A sample size of 1,500 patients will provide 88% power to demonstrate superiority of the capillary refill time-targeted strategy.

**Conclusions::**

If hemodynamic phenotype-based, capillary refill time-targeted resuscitation demonstrates to be a superior strategy, care processes in septic shock resuscitation can be optimized with bedside tools.

## INTRODUCTION

Early recognition and prompt reversion of sepsis-induced tissue hypoperfusion are key factors in determining the survival of patient experiencing septic shock.^(1,2)^ Notwithstanding extensive research, mortality due to septic shock remains substantially high, and there is no consensus about the best initial resuscitation strategy. Indeed, resuscitative interventions assuming the principle of *one size fits all* run the risk of unnecessary fluid administration and harmful volume accumulation.^(3)^

Recent evidence suggests that peripheral perfusionguided strategies during the early stages of septic shock might be associated with lower mortality, faster recovery of organ dysfunction and reduced intensity of therapeutic interventions compared with lactate-guided resuscitation.^(4,5)^ In fact, guiding resuscitation utilizing evaluation of peripheral perfusion with capillary refill time (CRT) resulted in a significant reduction in administered fluids and vasoactive-related interventions.^(6)^ This resuscitation strategy could also limit unnecessary therapeutic interventions performed in the presence of persistently high lactate levels.^(6)^ Thus, CRT has been proposed to guide resuscitation in the intensive care unit (ICU) and, potentially, in pre-ICU or resource- limited settings.^(2,7)^

Mechanisms involved in circulatory failure are complicated and frequently overlap in septic shock. Consequently, resuscitative interventions should be integrative and individualized according to particular macrohemodynamic features detected during clinical assessment.^(8)^ For example, some patients might remain hypovolemic even after initial fluid loading, which would suggest a potential benefit from additional volume administration.^(9)^ Others exhibiting very low diastolic arterial pressures (DAPs) could benefit from increasing the vasopressor dose instead of administering additional and potentially harmful fluid loading.^(10-12)^ Similarly, early identification of left/right ventricular dysfunction could lead to early hemodynamic adjustment to limit or avoid deleterious interventions.^(13)^ Therefore, a characterization of these cardiovascular phenotypes in septic shock might lead to more personalized resuscitation and improved outcomes. Despite extensive research, a universal method for the identification of such phenotypes has not yet been agreed upon.^(13-15)^

In an effort to characterize clinical and hemodynamic phenotypes in patients with early septic shock and thus target the most adequate therapeutic approaches, the ANDROMEDA-SHOCK-2 (A2) study will integrate different variables, such as the systematic assessment of fluid responsiveness, pulse pressure as a surrogate of stroke volume, DAP for evaluation of vascular tone, and selective echocardiography for assessment of myocardial dysfunction.^(10,13,16-18)^

We hypothesize that CRT-targeted resuscitation based on clinical hemodynamic phenotyping in patients with septic shock will improve a composite hierarchical outcome of mortality, time to cessation of vital support, and length of hospital stay within 28 days compared with standard care.

## METHODS

### Main objective

To determine whether CRT-targeted resuscitation based on clinical hemodynamic phenotyping is associated with a decrease in a hierarchical composite outcome within 28 days after randomization, which includes mortality, time to cessation of vital support, and length of hospital stay, compared to standard care in patients with early septic shock.

### Secondary objective

To determine whether CRT-targeted resuscitation based on clinical hemodynamic phenotyping is associated with a decrease in all-cause mortality within 28 days after randomization, more organ support-free days within 28 days after randomization, and a decreased length of hospital stay within 28 days after randomization compared to standard care in patients with early septic shock.

### Primary outcome

The primary outcome is a hierarchical composite of all-cause mortality, time to cessation of vital support (truncated at 28 days) and length of hospital stay within 28 days after randomization.

### Secondary outcomes

Secondary outcomes are: all-cause mortality within 28 days after randomization; organ support-free days within 28 days; and length of hospital stay (truncated at 28 days).

### Other (tertiary) clinical outcomes

Other clinical outcomes are: all-cause mortality within 90 days after randomization; length of hospital stay; length of ICU stay; time to cessation of vasopressor support; time to cessation of mechanical ventilation (MV); time to cessation of renal replacement therapy (RRT); vasopressor support-free days; MV-free days; RRT-free days; variation in Sequential Organ Failure Assessment (SOFA) score;^(19)^ variation in creatinine-based Kidney Disease: Improving Global Outcomes (KDIGO) stage;^(20)^ volume of resuscitation fluids; net fluid balance; Evolution of CRT; evolution of lactate levels; evolution of central venous pressure (CVP); evolution of central venous oxygen saturation (ScvO2); and evolution of the central venous to arterial carbon dioxide difference (delta pCO2(v-a))

### Study design

ANDROMEDA-SHOCK-2 will be a multicenter, open-label, investigator-generated, randomized controlled trial conducted under supervision of an independent Data Safety Monitoring Board (DSMB). Recruited patients will be randomized to CRT-P or to standard care.

### Patients

#### Inclusion criteria

Consecutive adult patients (≥ 18 years) with septic shock according to the Sepsis-3 consensus conference will be considered eligible. Septic shock is defined as suspected or confirmed infection and norepinephrine requirements due to persistent hypotension after a fluid load of at least 1000mL in 1 hour, plus the presence of hyperlactatemia (> 2mmol/L).^(21)^

#### Patients will be excluded based on the following criteria

We will exclude patients with: more than 4 hours since diagnosis of septic shock anticipated surgery or acute hemodialysis procedure to start during the 6-hour intervention period; active bleeding; do-not-resuscitate status; Child B-C cirrhosis; underlying disease process with a life expectancy < 90 days and/or the attending clinician deems aggressive resuscitation unsuitable; pregnancy; concomitant severe acute respiratory distress syndrome (ARDS); and patients in whom CRT cannot be accurately assessed.

Screening will be conducted in the ICU. Clinical investigators at each participating center will be responsible for screening all patients who fulfil the inclusion criteria. A screening log will be generated to register all patients with septic shock regardless of whether they are eligible for study inclusion.

### Randomization and blinding

A randomization sequence with a 1:1 allocation will be generated using a computer program and captured using an electronic data management system. Study group assignment will be performed by means of randomized permuted blocks of variable size. Allocation concealment will be maintained by means of central randomization.

Given that the intervention will be administered to critically ill patients (mostly sedated), blinding of these patients is not necessary. Because this is a nonpharmacological intervention, blinding the medical team is not feasible.

### Interventions

#### General management for both groups

Sepsis source identification and treatment should be pursued as a priority of first-line treatment. A central venous catheter and an arterial line will be inserted in all cases. The use of a pulmonary artery catheter or a pulsecontour continuous cardiac output device is not part of the CRT-P protocol but may be used in conditions in which attending physicians consider it for safety reasons.

Norepinephrine will be the vasopressor of choice and will be adjusted to achieve and maintain a mean arterial pressure (MAP) ≥ 65mmHg in all patients. Hemoglobin concentrations will be maintained at 7 - 8g/ dL or greater to optimize arterial O2 content. Stress ulcer prophylaxis, glycemic control, prophylaxis of deep venous thrombosis, and MV settings will be managed according to current recommendations.^(2)^ Rescue therapies, such as epinephrine, vasopressin analogs, and steroids, or different blood purification techniques, such as high-volume hemofiltration, in evolving patients will be administered according to the standard practice of each center.

### Study protocol

A sequential approach to resuscitation will be followed in the CRT-P group, as shown in figure 1. Time 0 is the starting point after randomization when a central venous catheter and an arterial line are already in place, and the basal measurements are performed, including hemodynamics and blood sampling. The study period will last 6 hours. Thereafter, attending physicians may continue to treat patients according to their standard practice or department protocol.

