### Capillary refill time assessment

Capillary refill time will be measured by applying firm pressure to the ventral surface of the right index finger distal phalanx with a glass microscope slide. The pressure will be increased until the skin is blank and then maintained for 10 seconds. The time for return of the normal skin color will be registered with a chronometer. A CRT > 3 seconds will be considered abnormal.^(4,32,33)^

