### Data collection and management

Study follow-up and the variables that will be collected are described in table 1.

**Table 1 t1:** Relevant variables to be registered during the study period

Baseline
Demographics, comorbidities, APACHE-II score, SOFA score
Sepsis source, treatment, adequacy of treatment, time from shock initiation to first antibiotics
Pre-ICU resuscitation administered fluid and fluid balance, AKI-KDIGO criteria^(19,20)^
Hemodynamics: HR, SAP, MAP, DAP, CVP, NE dose
Perfusion variables: lactate, ScvO2, delta pCO2(v-a), hemoglobin, CRT, mottling score

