The win ratio is calculated as the total number of wins in the experimental group divided by the total number of wins in the control group. A value greater than 1 indicates better outcomes in the experimental group. The bootstrap resampling method will be used to calculate the 95% confidence interval (95%CI) for the win ratio and P value for the hypothesis test.

We will assess the treatment effect on the primary hierarchical composite outcome according to the following subgroups: age (< or ≥ 65 years); APACHE II (< or ≥ 25 points); SOFA (< or ≥ 10 points); baseline lactate (< or ≥ 4mmol/L); baseline CRT (< or ≥ 3 seconds); septic shock source (lung *versus* abdominal *versus* urinary *versus* soft tissues *versus* bacteremia *versus* other); and MV at inclusion.

P values will be reported for the primary outcome analysis, and p values for interaction will be reported for the subgroup analyses; the remaining outcomes will be reported with the mean effect and 95%CI. Given the potential for type I error due to multiple comparisons, the findings for the analyses of the secondary and tertiary outcomes should be interpreted as exploratory. All tests are 2-sided with an α level of 0.05. All analyses will be performed with the latest version of R software (R Foundation for Statistical Computing).

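### Baseline CRT is read after randomization in an open-label trial, so the baseline CRT subgroup and any change from baseline in CRT are open to a shift by arm

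*Protocol article*

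**What the plan says.** All sections cited are in the protocol article.

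- **Timing.** Study protocol: "Time 0 is the starting point after randomization when a central venous catheter and an arterial line are already in place, and the basal measurements" (carried out at that point). The same sentence adds that they "are performed, including hemodynamics and blood sampling". It does not name CRT. Table 1 (Data collection and management) does, in its baseline block: "Perfusion variables: lactate, ScvO2, delta pCO2(v-a), hemoglobin, CRT, mottling score".
- **Role of the reading.** Under Intervention group (CRT-P), a normal baseline CRT leads to hourly monitoring and an abnormal one leads into the algorithm.
- **How CRT is measured.** Capillary refill time assessment: "The time for return of the normal skin color will be registered with a chronometer". Above 3 seconds is abnormal.
- **Blinding.** Study design calls the trial open-label. Randomization and blinding says that "blinding the medical team is not feasible". No section says who takes the baseline CRT or describes a blinded assessor.
- **Use in the analysis.** Statistical analysis lists among the subgroups for the primary outcome "baseline lactate (< or ≥ 4mmol/L); baseline CRT (< or ≥ 3 seconds"), with a p value for interaction. Evolution of CRT is a tertiary outcome.
- **Before randomization.** Eligibility requires lactate above 2 mmol/L and excludes "patients in whom CRT cannot be accurately assessed". No CRT value is required at that stage.

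**The concern.** A subgroup variable should be fixed before allocation, or at least be beyond its influence. Otherwise the patients in a stratum of one arm are no longer the counterparts of those in the same stratum of the other arm, and the comparison inside the stratum loses the protection of randomization.

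Baseline CRT is exposed in three ways. It is read after allocation. It depends on an observer's judgement of when colour has returned. In the CRT-P arm the protocol attaches an immediate consequence to it, and in standard care it attaches none. If borderline fingers are called abnormal more readily in CRT-P, lower-risk patients move into that arm's abnormal stratum and leave its normal stratum. Both strata can then favour CRT-P without any treatment effect (stage migration). This is the subgroup that readers of a CRT-targeted trial will look at first. A change from baseline in CRT inherits the same shift.

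**Working it through.** The plan gives no figure on this point. Its sample size and power do not depend on when baseline is measured. The check is therefore a reading of the sections, followed by an illustration of size.

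**Reading.** Study protocol puts the basal measurements at Time 0, after randomization. Table 1 makes CRT one of them. No section requires a CRT value before allocation, so an analysis plan could not recover one later.

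**Illustration 1: migration between strata, no true treatment effect.** From Sample size: mortality 39%. Assumed, not in the documents: half of patients truly abnormal; mortality 46% if abnormal and 32% if normal (0.5 × 46 + 0.5 × 32 = 39%); a share q of all CRT-P patients, with mortality m, read as abnormal although the same patients in the control arm would be read as normal.

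- Abnormal stratum in CRT-P = (0.5 × 0.46 + q·m)/(0.5 + q); control 46%.
- Normal stratum in CRT-P = (0.5 × 0.32 − q·m)/(0.5 − q); control 32%.

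| q | m | Abnormal, CRT-P | Spurious benefit | Normal, CRT-P | Spurious benefit |
|---|---|---|---|---|---|
| 0.05 | 0.39 | 0.2495/0.55 = 45.4% | 0.6 points | 0.1405/0.45 = 31.2% | 0.8 points |
| 0.10 | 0.39 | 0.269/0.60 = 44.8% | 1.2 points | 0.121/0.40 = 30.3% | 1.8 points |
| 0.10 | 0.32 | 0.262/0.60 = 43.7% | 2.3 points | 0.128/0.40 = 32.0% | 0 |

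With q = 0 every difference is zero. If the migration runs the other way, the sign reverses. For q = 0.10 and m = 0.39, the abnormal stratum becomes (0.23 − 0.039)/0.40 = 47.8% and the normal stratum (0.16 + 0.039)/0.60 = 33.2%, a spurious harm in both.

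**Illustration 2: a constant shift in the reading.** Assumed: lognormal CRT with mean 3.5 s (SD 1.5) or mean 4.5 s (SD 2.5); log-odds of death rising by 0.15 to 0.30 per second; overall mortality about 39%; no treatment effect; readings longer in one arm only.

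| Shift | Share at or above 3 s in the shifted arm (unshifted 57% / 70%) | Spurious difference, either stratum |
|---|---|---|
| 0.25 s | 65% / 75% | 0.5 to 1.4 points |
| 0.5 s | 73% / 81% | 1.0 to 2.7 points |
| 1.0 s | 88% / 90% | 2.0 to 4.7 points |

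The 0.25 s shift reclassifies about 5 to 8% of patients, close to the range in illustration 1, and gives a similar size. If only the baseline reading shifts, a change from baseline in CRT is off by exactly the shift.

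**Effect on the interaction test.** Illustration 1, on mortality rather than the win ratio, with 750 per arm: the control strata have 375 patients each. At q = 0.10 the CRT-P strata have 450 and 300. The variance of the contrast at m = 0.39 is 0.46 × 0.54/375 + 0.32 × 0.68/375 + 0.448 × 0.552/450 + 0.303 × 0.697/300 = 0.0025, so the standard error is about 5.0 points.

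- q = 0.10, m = 0.39: contrast 1.8 − 1.2 = 0.6 points; false-positive rate 5.2% at a nominal 5%.
- q = 0.05, m = 0.39: 5.0%.
- q = 0.10, m = 0.32: contrast 2.3 points; 7.5%.

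**The case against.** **Every input to the size is assumed.** This stands. The abnormal share, the mortality split and the amount of migration are not in the documents, and without differential reading there is no bias.

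**Unblinded staff take the reading.** A reader might take this as stated. It is an inference: the measurer is not named, and the text says only that the medical team cannot be blinded. Nor is the standard arm's reading necessarily without consequence, because Standard care group leaves perfusion monitoring and treatment to each site, and a site may act on CRT. A Manual of Operations exists and is not shown. The timing, however, is stated positively in the article.

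**The sentence could mean that the basal measurements are already complete by Time 0.** This is possible but less natural, and it still does not place them before allocation.

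**The interaction p value becomes uninterpretable.** This is tempting, but it does not follow. Similar spurious effects in both strata largely cancel in the contrast, as the false-positive rates above show. The damage is mainly to the estimates within strata.

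**All baseline values and all outcomes measured from baseline are biased.** The documents do not support this. Table 1 opens with "Demographics, comorbidities, APACHE-II score, SOFA score"; demographics and comorbidities cannot shift. An observer's expectation does not move lactate, ScvO2, delta pCO2 or creatinine. These could differ only if care diverged by arm between randomization and Time 0. The evolution outcomes are not defined as change from baseline, and they are tertiary and declared exploratory.

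**Conclusion.** The concern holds in a limited form. As written, baseline CRT is taken after allocation in an open-label trial, with no blinded assessor described, and knowledge of the arm could shift borderline readings. What is exposed is one pre-specified subgroup analysis of the primary outcome and any change from baseline in CRT.

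If 5 to 10% of CRT-P patients were reclassified, and under the stratum mortalities assumed above, the spurious difference in the affected strata is about 0.6 to 2.3 mortality points. It is zero if readings do not differ by arm. A reader might set this against the planned 6-point reduction and conclude that the trial's main result is at risk. It is not: the 6 points concern overall mortality, and neither the overall primary analysis nor the secondary outcomes use a baseline value. This is an inexpensive improvement to make before enrolment, since a CRT value never recorded before allocation cannot be recovered later.

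**What to change.** In the Study protocol section, require CRT, and the other subgroup variables already available (the eligibility lactate, SOFA, APACHE II, mechanical ventilation status), to be recorded in the electronic case report form before the central system releases the allocation. State in Statistical analysis that these values define the subgroups and serve as the CRT baseline. Measurements that need a line not yet placed may stay at Time 0, labelled as post-randomization.

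Leave the 6-hour study window as it is. Starting the fluid and hemodynamic window at randomization would separate it from the study period that begins at Time 0.

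The cost is a sentence in each section, an entry check in the case report form, and a few minutes of the 4-hour enrolment window. Lactate is already known from eligibility. Whether CRT can be assessed must already be judged for the exclusion, although the value itself would be a new requirement. Sample size and power do not change.

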**Figure 1 f1:**
[figure not shown]
Study protocol flow diagram. NE - norepinephrine; MAP - mean arterial pressure; CRT - capillary refill time; PP - pulse pressure; DBP - diastolic blood pressure; CCE - critical care echocardiography; FR - fluid responsiveness.

### Tests and procedures during the study period

#### Intervention group (CRT-P)

These patients should follow a management algorithm as described in figure 1.

Patients with normal CRT at baseline will proceed to periodic monitoring (every hour/6 hours) and start the algorithm if CRT becomes abnormal at any of these timepoints. Patients with abnormal CRT will follow the loop when fulfilling the Sepsis-3 definition of septic shock. The first categorization will be performed according to pulse pressure.^(16,17,22)^ Patients with a pulse pressure < 40mmHg, will undergo fluid responsiveness assessment.

Fluid responsiveness assessments will be performed using the technique preferred by each center, but supplementary recommendations with technical details will be provided in the Manual of Operations.^(9,23-26)^ Passive-leg raising with pulse pressure may be acceptable in spontaneous breathing patients. However, considering the possibility of false negatives, it is not the preferred technique.^(9,26,27)^

Fluid responsiveness-negative patients or those with undetermined status should proceed to obligatory critical care echocardiography (CCE) to rule out significant cardiac dysfunction (Figure 1) and proceed accordingly.^(28,29)^ Fluid boluses (500mL of crystalloids or 5% albumin) will be administered in 30-minute intervals with a maximum of 1000cc (2 fluid challenges) provided that the patient remains fluid responsiveness-positive and no safety issues appear (increase in CVP > 5mmHg or other congestion signals). Patients with safety signals should proceed immediately to CCE (Figure 1).

Patients with pulse pressure ≥ 40mmHg will follow the right arm of the algorithm (Figure 1) will proceed according to DAP. If DAP is ≥ 50mmHg, then the patient will move to fluid responsiveness assessment.^(10,30,31)^ If DAP is < 50mmHg, then norepinephrine will be increased to achieve a MAP > 65mmHg and a DAP ≥ 50 mmHg. Capillary refill time will be assessed 1 hour later. Norepinephrine will be increased in 0.1mics/kg/minute increments up to 0.5mcg/kg/minute. When reaching 0.5mcg/kg/minute, only a 25% additional increment will be acceptable if the DAP goal still has not been reached (max 0.625mcg/kg/minute). Norepinephrine may be stopped earlier if potential adverse effects are observed (heart rate - HR) > 130 bpm, arrhythmias, or evident cardiac ischemia). In centers in which vasopressin is part of the standard of care, it may be added when norepinephrine > 0.3mics/kg/minute, but up to a limit of 0.04U/minute to obtain a DAP ≥ 50mmHg.

If the CRT is normal, patients will proceed to periodic monitoring. Patients with persistent abnormal CRT or that has reached norepinephrine or vasopressin safety limit will proceed directly to CCE according to the results. Patients who correct CRT with first-tier interventions (fluid boluses on one side and norepinephrine adjustment in the other) will not be subjected to obligatory CCE but will simply proceed to periodic monitoring.

When a patient fails to correct CRT after the whole algorithm procedure, rescue therapies should be considered by attending physicians. These therapies will not be standardized since the protocol is interrupted at that point; however, monitoring and registration during the 6 hours intervention period and thereafter continues until the end of the study.

